### Standard of care

All study participants will receive the standard of care for disease management. They will attend clinical assessments quarterly for year 1 and biannually thereafter. Additional clinical visits are allowed per standard of care. The rationale for quarterly visits during the first year is two-fold: a period of sufficient duration to ensure slow-acting DMARDs take effect; a monitoring frequency conducive to detecting treatment adjustments over the early course of care for patients with newly-diagnosed RA or UIA. Pharmacotherapy will be monitored and adjusted over these clinical visits as per rheumatologist-dependent standard of care. Pharmacotherapeutic management of RA and UIA is modified based on monitoring a combination of clinical, laboratory, and diagnostic imaging assessments, in conjunction with patient therapeutic goals. Intra-articular or systemic corticosteroid therapy may be used per standard of care and will be documented. Generally, standard of care may vary by rheumatologist. As a result, the treating rheumatologist is included as a parameter in the minimization treatment allocation scheme.

Study rheumatologists will receive baseline MRI and X-ray reports for all study participants. Upon requisition of extra-study X-ray, the radiology report for the last study-derived images will be made available to the treating rheumatologist per standard of care, regardless of treatment allocation. In contrast, MRI is not standard of care for any of the study investigators and will not be provided. If no progression occurs between diagnostic imaging intervals, or if the participant is allocated to the standard of care intervention arm, negative diagnostic imaging reports will be reported to the treating physician.

As a historical control of standard of care, a chart audit of a randomly selected sample of study-eligible patients visiting the study rheumatologists 3 years preceding study enrolment will be conducted. The chart audit will be used to determine the frequency of diagnostic imaging requisition and treatment escalation. Rates of diagnostic imaging and treatment escalation between the study and historical control will provide a measure of standard of care bias in the study [60] - that is, to determine if either diagnostic imaging or treatment escalation occur more or less frequently within the study than in clinical practice for the same setting.

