### Statistical analysis

#### Sample size

A sample size of 186 RA and UIA patients was estimated from a one-way analysis of variance statistical test to determine a difference in the rate of pharmacological treatment escalation between imaging interventions over 2 years between three groups with intermediate dispersion of data [74].

(3)$$f=\frac{d}{2}\sqrt{\frac{\left(k+1\right)}{3\left(k-1\right)}}$$

where *f* is the analysis of variance effect size; *k* is the number of groups being compared; and *d* is the standardized effect size,

(4)$$d=\frac{\delta }{s}$$

where, *δ* is the difference between the greatest and least group mean; and *s* is the standard deviation.

This parametric test is sufficiently robust to yield sample size estimates for non-parametric data [74].

Treatment escalation was assumed to be directly proportional to disease progression. The rate of X-ray progression over 2 years [75] was taken together with 1-year MRI and X-ray progression data [15] to estimate testing between 36% MRI progression of the second to fifth MCPs joints of a single hand, 25% radiographic progression of bilateral hands and wrists, and no progression for the standard of care group. Although some patients may progress several-fold over the clinically relevant threshold, progression was conservatively assumed to result in a single pharmacological treatment escalation per affected participant, since a change in therapy is expected to introduce an incremental protective effect.

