First, the study population includes patients with varying degrees of disease activity. This may cause background noise to the signal of the intervention. The evidence that 19% of RA patients in clinical remission progress on diagnostic imaging over 1 year [17] may be limited to a small proportion of patients in clinical practice with quiescent disease. For the remainder of patients with active disease, treatment decision-making based on standard of care disease activity findings may be sufficient. In the presence of clinically active disease, attempts to link the effect of diagnostic imaging evidence of disease progression on treatment escalation may be confounded. The signal from the intervention may be dampened by the noise associated with standard of care treatment escalation. Ideally the study population would be characterized by a treat-to-target standard of care and limited to patients with low disease activity or in clinical remission to minimize the effect of standard of care on treatment escalation. In this trial setting, where the clinical practice use of disease activity measures is limited [40], the potential impact of diagnostic imaging guided care may be magnified.

Second, the application of the SDD has some limitations. In the current study, the inter-rater SDD will be used for simplicity. The SDD was used given that all image sets are to be scored independently. With the well characterized scoring systems used, the independent scoring of individual image sets carries less potential for bias from sources both known and unknown. The SDD will also be assessed at two separate time points to account for changes in inter-rater reliability and hence SDD over time. The approach does not account for intra-rater reliability. In addition, the lack of pairing image sets for the same patient may result in less sensitivity to change compared to alternatives. The smallest detectable change (SDC) is an alternative approach that uses paired images to assess reliability and change. Use of the SDC produces less variability, enabling smaller differences in disease progression to be detected [60]. Implementation of the SDC also carries incremental logistical complexity (for coordinating pairing) and rater scoring time. Acknowledging these tradeoffs, the SDD was proposed for the current investigation.

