Third, for the sample size calculation, rates of disease progression were conservatively estimated from literature reports of disease progression between MRI and X-ray. Standard of care treatment escalation and a clinically meaningful effect size were not specifically accounted for in the estimate. Despite this limitation, the authors considered the sample size to be sufficient to resolve any incremental benefit of the interventions in the study population investigated.

A number of factors are expected to impact the relative merits of MRI and X-ray as prognostic tools in IA, including those affecting image resolution (for example, magnet strength to bore diameter ratio for MRI; number of views for radiography) and stage of disease. Measurement considerations including number of raters involved, their qualification and experience, number of readings and raters per image set, independent versus paired image rating, blinding the chronological order of image acquisitions, and current anti-rheumatic therapy are expected to affect the MRI and X-ray interventions equally.

This study represents an initial investigation into the clinical utility of MRI and X-ray in guiding anti-rheumatic pharmacotherapeutic decision-making for IA. The work will contribute to the knowledge of how diagnostic imaging may be leveraged to optimize rheumatologic care. Pending findings, future work will investigate the optimization of this intervention strategy, including but not limited to identifying population subsets at greatest risk, adjusting the interval over which imaging is conducted, testing in conjunction with a specific intensive DMARD clinical management strategy, and automated abnormality detection and quantification.

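### The stated 90% power is not supported for the primary endpoint as defined, because the sizing leaves out treatment escalation under standard of care and its variance

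*Protocol article*

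**What the plan says.** The sample size was "estimated from a one-way analysis of variance statistical test to determine a difference in the rate of pharmacological treatment escalation" between three groups. The section adds: "Treatment escalation was assumed to be directly proportional to disease progression". The rates entered are "36% MRI progression of the second to fifth MCPs joints of a single hand", 25% on X-ray, "and no progression for the standard of care group", with one escalation per progressing patient. The standard deviation is derived from progression-related escalation. With δ ≈ 0.46, s ≈ 0.58 and f ≈ 0.33, the section arrives at about 45 per group. It inflates this to 62 for remission, missing data and attrition, and states 90% power at the 5% level. The abstract repeats the 90%.

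Under Primary outcome, the endpoint is any change in DMARD agent or dose escalation, with no restriction on the reason. Under Standard of care: "Pharmacotherapy will be monitored and adjusted over these clinical visits as per rheumatologist-dependent standard of care". This applies to all arms.

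The Discussion warns: "The signal from the intervention may be dampened by the noise associated with standard of care treatment escalation". Among the limitations it states: "Standard of care treatment escalation and a clinically meaningful effect size were not specifically accounted for in the estimate". The next sentence says that "the authors considered the sample size to be sufficient to resolve any incremental benefit of the interventions in the study population investigated".

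**The concern.** The quantity sized and the quantity to be analysed differ. The calculation describes escalation caused by a progression report, which is zero in the sham arm by construction. The endpoint describes escalation from any cause. Patients qualify through swollen joints, a positive squeeze test or morning stiffness, and they are seen quarterly in year 1, so some escalation unrelated to the study reports must be expected in every arm.

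That background can cost power in two ways. If the endpoint is whether a patient escalated at all, a progression report adds nothing in a patient who has already escalated, so the arms move closer together. If escalations are counted, the increments survive but background variance is added to the noise.

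A non-significant result would be read against a stated 90% power and could be taken as evidence that imaging feedback does not change treatment, when the power for this endpoint has not been established.

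**Working it through.** **Inputs from the article.** Arm rates 0, 0.25 and 0.36; δ = 0.46; s = 0.58; k = 3; α = 0.05; 5% spontaneous remission; 15% missing data; 5% attrition per year; Kruskal-Wallis as the planned test (Analysis section). **Assumed:** the standard-of-care escalation rate, which the article does not give.

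**1. The plan's own figure.** d = 0.46/0.58 = 0.793. f = (0.793/2) × √(4/6) = 0.324, against a stated 0.33. For 90% power the noncentral F distribution gives 42 per group at f = 0.324 and 40 at f = 0.33. The stated 45 is slightly generous, with power 0.925 to 0.934. Inflation: 45/(0.95 × 0.85 × 0.90) = 61.9, so 62 is reproduced. On its own inputs the calculation therefore reaches 90%. The question is whether those inputs fit the endpoint.

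**2. Any escalation, yes or no.** Let b be the background rate, with imaging escalating 25% and 36% of patients not otherwise escalated: p = b + (1 − b) × {0, 0.25, 0.36}. Kruskal-Wallis on a binary outcome is in effect a 2-df chi-square test, with noncentrality λ = n Σ(pᵢ − p̄)² / [p̄(1 − p̄)].

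Example, b = 0.20 and n = 45: p = 0.20, 0.40, 0.488; p̄ = 0.3627; Σ(pᵢ − p̄)² = 0.04356; λ = 45 × 0.04356/0.2311 = 8.48; power 74%.

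| Background b | Arms (sham / X-ray / MRI) | Power, 45 evaluable | Power, all 62 evaluable |
|---|---|---|---|
| 0% | 0 / 25 / 36% | 98% | 99.7% |
| 10% | 10 / 32.5 / 42.4% | 89% | 96% |
| 20% | 20 / 40 / 48.8% | 74% | 87% |
| 30% | 30 / 47.5 / 55.2% | 59% | 74% |
| 50% | 50 / 62.5 / 68% | 34% | 45% |

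Simulation of the same model at 45 per arm agrees within about 4 points (93% at b = 10%, 77% at 20%, 60% at 30%, 33% at 50%).

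**3. Number of escalations, Kruskal-Wallis.** A random background count with the mean shown is drawn for every patient, and one further escalation is added with probability 0, 0.25 or 0.36. The full increments are kept.

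| Background mean over 2 years | Power, 45 evaluable | Power, all 62 evaluable |
|---|---|---|
| 0.25 | about 74% | about 88% |
| 0.5 | about 51% | about 65% |
| 1.0 | about 29% | about 36% |

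Simulation error and the choice of a Poisson or an overdispersed background move these by about two points.

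**4. The plan's own ANOVA with background variance added.** Keep δ = 0.46 and add a Poisson background of mean 0.5: s = √(0.58² + 0.5) = 0.915, f = 0.205, power at 45 per arm 55%.

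**5. The favourable case.** Keep the full 25- and 36-point differences on a binary endpoint: p = b, b + 0.25, b + 0.36. Power at 45 per arm is 89% to 94% for b from 10% to 50%. At b = 50% this requires imaging to escalate 0.25/0.50 = 50% and 0.36/0.50 = 72% of the remaining patients.

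**The case against.** The strongest reply is that ANOVA power depends on δ and s and not on the level in the control arm. On this view the zero is only a reference level for the imaging-driven increment and does not claim that nobody in the sham arm escalates. If the full differences survive, power stays near 90% (step 5). The stated s of 0.58 is also generous: s² = 0.336, against an average binary variance for 0/25/36% of (0 + 0.1875 + 0.2304)/3 = 0.139. The Discussion discloses the omission, and it also argues that limited use of disease activity measures in this setting may magnify the effect of imaging.

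Part of this stands. A reader might infer that the trial does not have 90% power, or that its real power is less than half of that. The documents do not support either reading, because the size of the loss depends on a standard-of-care rate they do not give, and at a background of about 10% power remains near 90%.

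The rest does not rescue the figure. Keeping the full differences on a binary endpoint needs imaging to act on a larger share of the remaining patients than the 25% and 36% the plan assumes. On counts the differences are kept by construction and power still falls. The slack in s does not absorb the background either (step 4). The disclosure gives no range, and the assurance that follows it rests on no figure.

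**Conclusion.** The point holds as a lack of support for the 90% figure, not as proof of a particular lower power. The sizing sets standard-of-care escalation to zero and uses progression-related variance only, while the endpoint counts every escalation in arms where therapy is adjusted throughout. At 45 evaluable per arm, power stays near 90% only if background escalation is about 10% or less, or if the full absolute differences survive on a binary endpoint. At background rates of 20% to 50% it is about 74% down to 34%, or 87% down to 45% if all 62 are evaluable. These ranges rest on an assumed background rate, on the plan's own 25% and 36%, and on imaging acting independently of the background.

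**What to change.** In the abstract and the Sample size section, replace the unqualified 90% statement with power, or the smallest detectable difference, for the planned Kruskal-Wallis test across a stated range of standard-of-care escalation rates. State whether escalation is analysed as yes/no or as a count, since the two lose power differently. The chart audit described under Standard of care is meant to yield historical escalation frequencies and can anchor the range once its results are available. In the Discussion, delete the sentence calling the sample sufficient, or qualify it by reference to that range.

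The cost is a recalculation and a few sentences. The stated power becomes less favourable. Recruitment, endpoint and analysis are unchanged, and no extra patients are needed.

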**Methods:**

A double-blind, randomized controlled trial has been designed. Rheumatoid and undifferentiated inflammatory arthritis patients will undergo an MRI and X-ray assessment every 6 months. Baseline adaptive randomization will be used to allocate participants to MRI, X-ray, or sham-intervention groups on a background of standard of care. Prognostic markers, treating physician, and baseline DMARD therapy will be used as intervention allocation parameters. The outcome measures in rheumatology RA MRI score and the van der Heijde-modified Sharp score will be used to evaluate the MRI and X-ray images, respectively. Radiologists will score anonymized images for all patients regardless of intervention allocation. Disease progression will be determined based on the study-specific, inter-rater smallest detectable difference. Allocation-dependent, intervention-concealed reports of positive or negative disease progression will be reported to the treating rheumatologist. Negative reports will be delivered for the sham-intervention group. Study-based radiology clinical reports will be provided to the treating rheumatologists for extra-study X-ray requisitions to limit patient radiation exposure as part of diagnostic imaging standard of care. DMARD treatment dose escalation and therapy changes will be measured to evaluate the primary objective. A sample size of 186 (62 per group) patients will be required to determine a 36% difference in pharmacological treatment escalation between the three groups with intermediate dispersion of data with 90% power at a 5% level of significance.

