The estimated standard deviation around disease progression-related treatment escalation rates was assumed to vary proportionally the variance around disease progression. From Emery and colleagues (2009), an average standard deviation of 5% greater magnitude than the mean progression was determined for group sample sizes of approximately 200 [75]. Standard deviation is inversely related to . A sample size 25% greater than the mean effect size reported in Emery was estimated here. Therefore, *δ* ≈ 0.46 and *s* ≈ 0.58, *f* ≈ 0.33. This represents a sample size of ≈ 45 per group [74] unadjusted for spontaneous remission, attrition and missing data. Despite the liberal inclusion criteria used here, with the current setting characterized by patients with significantly progressed symptom duration, spontaneous remission was conservatively estimated at 5%. Missing data and annual attrition were estimated to be 15% and 5%, respectively. Given these estimates, a sample size of 62 participants per intervention allocation group will be required to determine a 36% difference in the rate of treatment escalation with 90% power at a 5% level of significance [74,76]. A total of 186 IA patients will be recruited by six participating rheumatologists.

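### The printed sample-size inputs contradict each other: the assumed arm rates make δ 0.36, the calculation uses 0.46 with s ≈ 0.58, and the power is then claimed for 36%

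*Protocol article*

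**What the plan says.** The Sample size section states that the total of 186 "was estimated from a one-way analysis of variance statistical test to determine a difference in the rate of pharmacological treatment escalation" over two years, with three groups and intermediate dispersion. It defines f = (d/2)·√[(k+1)/(3(k−1))] and d = δ/s, where δ "is the difference between the greatest and least group mean".

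The assumed rates in the two imaging arms are "36% MRI progression of the second to fifth MCPs joints of a single hand, 25% radiographic progression of bilateral hands and wrists". For the third arm the section assumes "no progression for the standard of care group". To move from progression to escalation, "progression was conservatively assumed to result in a single pharmacological treatment escalation per affected participant".

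The same section takes the SD of escalation to vary in proportion to the variability of progression, citing an SD about 5% larger than mean progression in a published trial. It then prints: "Therefore, *δ* ≈ 0.46 and *s* ≈ 0.58, *f* ≈ 0.33". This is said to give about 45 per group, raised to 62 for 5% spontaneous remission, 15% missing data and 5% annual attrition.

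For 90% power at 5% significance, the section concludes that "a sample size of 62 participants per intervention allocation group will be required to determine a 36% difference in the rate of treatment escalation". The Methods part of the abstract says that 186 patients "will be required to determine a 36% difference in pharmacological treatment escalation between the three groups".

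**The concern.** With arm rates of 36%, 25% and 0 and one escalation per progressing participant, the greatest minus the least group mean is 0.36. No pair of assumed arms differs by 46 points, and no legible sentence turns 0.36 into 0.46. The calculation is therefore run on one difference and reported for a smaller one.

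This is the only power statement for the primary endpoint, and it stands in the abstract. A reader of a null result would take it that a 36-point effect had been sought with 90% power. The printed inputs do not support that reading, and they do not show which of δ, s or the 36% should change.

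**Working it through.** **Inputs (Sample size section).** k = 3; arm rates 0.36, 0.25, 0; printed δ ≈ 0.46, s ≈ 0.58, f ≈ 0.33; about 45 per group before losses and 62 after; power 90%, α = 5%. With k = 3 the article's formula becomes f = (δ/s)/2 × √(4/6) = 0.408 × δ/s. Power below is exact one-way ANOVA power from the non-central F distribution.

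**1. Reproducing the plan's figures with δ = 0.46.**
- f = 0.408 × 0.46/0.58 = 0.324. This needs 42 per group for 90% power, and power at 45 is 92.5%. Rounding in δ and s raises the requirement to 43, and allowing for Kruskal-Wallis efficiency (42/0.955) raises it to 44. The printed 45 is thus close.
- Losses: 45/(0.95 × 0.85 × 0.95²) = 45/0.729 = 61.7, so 62. This step is correct.

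The figure of about 45, as printed, rests on 0.46.

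**2. δ from the plan's own definition.** 0.36 − 0 = 0.36.

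**3. Power for δ = 0.36 under each candidate s.**

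| s | Basis | f | n per group for 90% | Power at 45 | Power at 62 |
|---|---|---|---|---|---|
| 0.58 | as printed | 0.253 | 67 | 74.4% | 87.6% |
| 0.50 | ceiling for a 0/1 outcome | 0.294 | 50 | 87% | 95% |
| 0.4725 | 0.36 × 1.05 × 1.25 | 0.311 | 45 | 90.3% | 97% |
| 0.45 | 0.36 × 1.25 | 0.327 | 41 | 93% | 98% |
| 0.373 | pooled SD at the stated rates | 0.394 | 29 | about 99% | above 99% |

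- Row 1: 67 evaluable would mean 67/0.729 = 91.9, about 92 randomised per group. The difference detectable with 90% power at 45 is 0.44. Using the three means directly (their SD is 0.151, so f = 0.151/0.58 = 0.260) gives 76.6% at 45 and 89.2% at 62, so the intermediate-dispersion shortcut does not drive the result.
- Rows 3 and 4: the printed pair has s/δ = 0.58/0.46 ≈ 1.26. Carrying a ratio of 1.25 to δ = 0.36 gives 0.45. The product 0.36 × 1.05 × 1.25 is an inference from the section's 5% and 25% figures; the article does not state it.
- Row 5: with one escalation per progressing participant the modelled outcome is 0/1, with variance p(1−p). The pooled SD is √[(0 + 0.25×0.75 + 0.36×0.64)/3] = √[(0 + 0.1875 + 0.2304)/3] = 0.373.

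**4. Is s ≈ 0.58 compatible with the model?** For a 0/1 outcome, p(1−p) is at most 0.25, so the SD is at most 0.5. The printed 0.58 lies outside that range.

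**The case against.** The best counter-argument is that the 74% corrects δ but leaves s alone, although the section ties s to progression. If both are scaled to 36%, s is about 0.45 to 0.47, power at 45 is about 90 to 93%, and the 36% and the 62 per group both survive. The 0/1 model points the same way, because it excludes s = 0.58 altogether. Also, in the text available here a term is missing from the sentence on how the SD scales, and the cited sources are not shown, so it cannot be settled which printed number is wrong.

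Most of this stands. A reader might infer that the trial is underpowered at 74%, or that it needs about 92 per group. The documents do not support that: both figures hold only if s ≈ 0.58 is right, and the section's own assumptions speak against it.

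It does not remove the contradiction. The definition of δ, the three rates, the printed δ and s and the 36% are all legible and conflict whatever the missing term was. The section's 25% figure does not rescue 0.46 either: 0.36 × 1.25 is 0.45, and an inflated δ would make the 36% claim wrong instead. The Discussion concedes that standard-of-care escalation and a clinically meaningful effect were not accounted for, but it does not mention this mismatch.

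**Conclusion.** The stated basis for the power claim is wrong as written. By the article's own definition δ is 0.36, while the calculation uses about 0.46 and reports the result for 36%. The consequence depends on s:

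- If s ≈ 0.58 is kept, power for 36 points is about 74% at 45 evaluable per group (88% if all 62 are analysed), and 90% power at 45 applies to about 44 points.
- If s scales with progression (0.45 to 0.47), power at 45 is about 90 to 93% and 62 per group stands, but the printed δ and s are both wrong.
- If s follows from a 0/1 escalation at the stated rates (0.37), power at 45 is about 99%.

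The inconsistency is established; a shortfall in sample size is not. All figures assume the article's ANOVA formula, three equal groups, its assumed rates and α = 5%.

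**What to change.** Reconcile δ, s and the 36% in the Sample size section and in the abstract:

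1. Set δ = 0.36, in line with the definition and the arm rates.
2. State an s consistent with the assumed outcome and say how it was obtained. If participants may have more than one escalation, so that s can exceed 0.5, say so and change the single-escalation assumption to match.
3. Recompute f, n per group and power from those inputs and print them.
4. Only if s ≈ 0.58 is justified and retained, restate the claim as about 74% power for 36 points, or 90% power for about 44 points, at 45 evaluable per group.

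The cost is a few corrected numbers and one power sentence in two places. The correction itself needs no extra patients.
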